**Fig. 3 Fig3:**
[figure not shown]
Skin transfers. Image shows a skin transfer applied near to the wound(s) to promote adherence to the randomised dressing allocation

### Study centres and surgeons

Four NHS Hospital Trusts are taking part, one of which is recruiting participants having either abdominal surgery or Caesarean section. (Three Trusts had agreed to take part at the outset and a fourth Trust, recruiting patients having abdominal surgery, joined in month 6.) All general surgical teams carry out a wide range of operations. The participating obstetric unit carries out about 1800 Caesarean sections each year. Since the operations are all being carried out as part of the usual care of participants, there are no restrictions on operating personnel or ward care.

### Primary outcome

The primary outcome is successful screening of a participant, determination of the participant’s eligibility and consent to be randomised in the pilot trial, at the time of randomisation. This information, together with the denominator describing the total number of participants approached, will establish whether recruitment into the main trial is possible.

### Secondary outcomes

These will include:Adherence to disclosure of dressing category allocation at the designated timeAdherence to the allocated dressing type by the usual care team during the index hospital admission and, if applicable, reason for non-adherenceQuality and completeness of the data for different outcomes anticipated to be measured in the main trial (see below; assessed at different times), including component assessments contributing to an overall judgement about the occurrence of a SSIAdherence to the follow-up scheduleDocumentation of co-interventions (e.g. details of hair removal, use of skin cleansing agents, type of wound closure methods, prescription of prophylactic antibiotics) and classification of surgery as ‘clean’, ‘contaminated’ or ‘dirty’ at the time of the operationCompletion of the reference SSI assessment at 4–8 weeks by a blinded observerCompletion of a wound healing questionnaire (WHQ [18] at 4–8 weeks by a blinded observer and by the participantCompletion of a wound management questionnaire (WMQ; developed during Phase A) up to 4 days after randomisation by an observer or the participant (if discharged early, e.g. day-case surgery)Completion of a wound experience questionnaire (WEQ; developed during Phase A) up to 4 days after randomisation by the participantAssessment of wounds from digital photographs at 4–8 weeks, if submitted

Bluebelle is a feasibility study and some of these secondary outcomes were developed in Phase A and are being piloted in Phase B. Therefore, detailed scoring methods are not currently available. We will report the questionnaire response rates, the number of fully completed questionnaires and rates of missing items in this pilot RCT as part of the evaluation of the acceptability of the new questionnaires to patients. The data from the pilot trial are also being used to validate some of the questionnaires.

### Anticipated outcomes in a subsequent main trial

The following outcomes are expected to be assessed in a main trial; the ability to collect these outcomes is, therefore, a key focus of the pilot trial:Occurrence of a SSI up to 4–8 weeks after randomisation (primary)Wound management questionnairePatient reported outcomes: wound experience questionnaire, documenting symptoms and experiences of the wound and dressings, and generic health status, assessed by the EQ-5D-5L [22]Wound complications arising up to 4–8 weeks after randomisationResource use up to 4–8 weeks, including length of postoperative hospital stay, rates of re-admission and duration

### Trial procedures and data collection up to four days after randomisation

The schedule of data collection is described in the SPIRIT Figure (Fig. 2).

Surgery and closure of wounds takes place as per usual practice. A member of theatre personnel, or research team, records: (1) the time taken to close the wound; (2) use of laparoscopic or open surgical methods; and (3) the method of wound closure. A member of theatre personnel or research team may also take one or more digital photographs of the wound(s). If randomised to disclosure of allocation after wound closure, the time of completing wound closure must be entered into the database to obtain the allocation. A range of methods are being used to promote adherence to the randomised dressing allocations in hospital, adapted to the circumstances of participating hospitals. These include simple labels, to be attached to medical notes or placed by the bedside, as well as skin transfers (Fig. 3).

Up to four days after surgery, after any early wound care that is required, a healthcare professional completes the WMQ. This questionnaire captures information about aspects of the participant’s wound management. If discharged early, e.g. after day-case surgery or the day after surgery, the research team gives the participant the WMQ to complete by day 4 and send back to the trials unit in a pre-paid envelope.

The local research team gives each participant the WEQ to complete up to four days after surgery. For participants who are in hospital at this time, the WEQ is collected by the research team. If discharged early, e.g. after day-case surgery or the day after surgery, the participant completes the WEQ at home by day 4 and sends it back to the trials unit in a pre-paid envelope.

### Data collection up to 4–8 weeks after randomisation

Local research teams give each participant a copy of the EQ-5D-5L and a pre-paid reply envelope to take home and instruct them to complete and return it if a wound becomes infected or problematic. The reason for asking for the EQ-5D-5L to be completed is to try to document the peak impact of a wound problem on health status to inform a future health economic evaluation.

Several follow-up assessments are required 4–8 weeks after randomisation. First, the participant needs to complete a copy of the EQ-5D-5L and the WHQ; these questionnaires can be given to participants at discharge from hospital or posted shortly before they fall due. Around this time, participants who have agreed to send a photograph may also be sent an email or text message including a web-link that allows them to upload a photograph securely. Then, a blinded health professional needs to complete the WHQ; this can be done face-to-face, typically at the same clinic attendance but before the reference SSI assessment, or administered by telephone. Finally, the face-to-face reference SSI assessment is completed by a blinded health professional, who must be different to the one completing the WHQ; this assessment includes eliciting information about potential wound-related complications. Whenever possible, the face-to-face clinic visit is arranged to coincide with a usual care clinic appointment. When this is not possible, travel expenses are offered to the participant. For women who have had a Caesarean section, the WHQ questionnaire is administered by telephone and research midwives then carry out the reference SSI assessment at a home visit.

To promote retention, reminders are sent out to participants who fail to return postal questionnaires promptly. Participants who fail to attend for the face-to-face SSI assessment are offered further appointments.

### Source data

The operation and medical notes, and other information held electronically on hospital information systems, provide source data for participant demographic and baseline information, operation details and postoperative morbidity. The completed participant questionnaires and observer-reported assessments of SSI and wound management are the primary data source for these measures. The data source for secondary adverse outcomes will be the participant’s medical notes. Wound photographs are the primary data source for this outcome.

Staff at participating centres record data on paper CRFs, then use a password-protected web server application to transcribe the data into a custom-designed database, located on a secure NHS server. The database has validation on data fields.

### Assessment and analysis of resource use

The pilot trial will assess the feasibility of collecting healthcare resource use data from the CRFs completed during the admission and at the 4–8 week follow-up. Relevant resource use is expected to fall under the following categories:The wound dressing itselfPostoperative resources expended in the hospital settingSSI-related carePost-discharge resources expended in primary care

The analysis will involve an assessment of the quality and completeness of the data for each data item, for example data on type of wound dressing and frequency of use, and other data on healthcare services provided in the hospital setting (i.e. post-randomisation hospital stay and follow-up outpatient appointments to assess wound healing). It will also start to consider the main drivers of cost, so that these can be accurately collected within the main trial.

Unit cost information associated with different types of care will be collected or estimated in preparation for the main trial and to ensure that these costs are available or can be generated. Particular attention will be paid to understanding the costs associated with SSIs as preliminary modelling suggests that these costs, rather than the costs of dressings, are likely to be the main driver of any cost differences between the arms of the trial. Preference-based quality-of-life estimates for the entire cohort will be derived by translating patients’ responses to the EQ-5D-5L over the 4–8 weeks after randomisation into utility values using the latest value set for England [23].

### Trial duration

The trial is timetabled to take up to 11 months, randomising the target number of 330 participants in nine months and then following up the last participants for 4–8 weeks.

### Sample size

A pilot study of 920 eligible participants, will allow a recruitment rate of 36% (corresponding to the target number randomised of 330) to be estimated with a 95% confidence interval (CI) of 32–39, and a recruitment rate of 60% with 95% CI of 56–64. For the simple dressings group, we anticipate an adherence rate of 90%. Assuming a 36% recruitment rate and 110 randomised participants per group, a 90% adherence rate will be estimated with a 95% CI of 82–95. We have no information on which to base any estimate of adherence in the no dressing and glue-as-a-dressing groups. However, if adherence were less than 70% in either group, we would conclude that randomisation to the group in question in the main trial would not be feasible.

### Statistical analyses

Summary descriptive statistics to inform plans for the main trial will be reported including:The number of potentially eligible participants per month per centreThe percentage of these potential participants confirmed as eligibleThe percentage of participants agreeing to be randomly allocated to dressing type in the pilot RCTThe percentage of randomised participants receiving the allocated treatment and completing outcome measurements at the 4–8-week assessmentRate of, and reasons for, non-adherence to allocation at both a wound and participant levelMean number of wounds per participantMean (or median if skewed) time from wound closure to randomisationMean (or median if skewed) time to complete randomisation processCompleteness of data items and reasons for missing dataRate of unblinding of outcome assessors and reasons for unblindingSecondary outcome measures relating to wound closure will be compared between groups, if the data allow

Only the statisticians will have access to the data. The analysis population will include all randomised participants. Results will be described by centre and by specialty as well as overall. If the data allow, subgroup analyses of the secondary outcome measures relating to wound closure will estimate the interaction of timing of randomisation by dressing group.

The primary analysis will take place when follow-up is complete for all recruited participants. During the pilot trial, we are monitoring recruitment and adherence periodically. The study steering committee will review safety data. In any interim reports, for example about withdrawals after randomization, the data will be presented by group with uninformative labels to keep the allocation masked.

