### Randomisation

Participants are randomised to one of three dressing groups. Participants are also randomised to disclosure of the dressing group allocation to the surgeon before wound closure or after wound closure. These two randomisations create six groups (Fig. 1). Both randomisations are in blocks of varying size and stratified by hospital Trust and specialty (abdominal surgery/obstetric surgery). The sequences of random allocations were generated by computer in advance of starting to recruit. Local research team members access a participant’s allocation via the Internet. The allocation is concealed until a participant’s eligibility and consent have been documented and information to identify the participant uniquely has been entered.

At the beginning of the operation, a member of the local research team (trainee or consultant surgeon/research midwife or nurse) logs on to the randomisation website (within the study database) using a secure password-protected computer system and enters the information needed to proceed to randomise the participant. Depending on the randomisation result, the dressing group allocation is disclosed immediately or the user is advised to log back into the website after the wound has been closed and enter the time of wound closure, after which the allocation is disclosed.

The second randomisation, the disclosure of allocation before or after wound closure, relates to objective 2. During preliminary discussions about the trial, the trials unit proposed that randomisation should occur after wound closure, to prevent surgeons closing the wound in different ways depending on the allocation, but surgeons considered that this would be problematic. The second randomisation allows the trial to test the feasibility of randomising after wound closure to be tested. Moreover, if photographs of the closed wound can be obtained in the operating theatre and subsequently assessed for the quality of wound closure, the effect of timing of randomisation on wound closure can be investigated.

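### The planned timing-by-dressing interaction on wound closure has twice the variance of the before-closure dressing contrast, which targets the same quantity if disclosure timing is kept

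*Protocol article*

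**What the plan says.** The Randomisation section describes two randomisations. Besides dressing type, "Participants are also randomised to disclosure of the dressing group allocation to the surgeon before wound closure or after wound closure", and "These two randomisations create six groups (Fig. 1". In the after-closure arm the user is instructed as follows: "log back into the website after the wound has been closed and enter the time of wound closure, after which the allocation is disclosed". As its reason, the article gives a worry that surgeons might close wounds differently according to the allocation. The section adds that, if theatre photographs can be obtained and assessed, "the effect of timing of randomisation on wound closure can be investigated". Objective 2 (Aims and objectives) includes the risk of performance bias from revealing the allocation before closure.

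The Statistical analyses section has two statements on closure, both conditional on the data being adequate. One says that closure outcomes will be compared across groups, without saying which groups. The other says that "subgroup analyses of the secondary outcome measures relating to wound closure will estimate the interaction of timing of randomisation by dressing group". The dressing contrast within the before-closure arm is not named.

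The Sample size section rests on the precision of recruitment and adherence rates. No power is claimed for closure. Keeping to the assigned disclosure time is a secondary outcome, and the theatre photograph needs separate, optional consent.

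**The concern.** The interaction is the dressing difference in the before-closure arm minus the dressing difference in the after-closure arm. The design fixes the true value of the second term at zero, provided disclosure happens when it should. Estimating a quantity already known to be zero, and subtracting the estimate, leaves the target unchanged and adds variance.

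At stake is how much the pilot can say about whether knowing the allocation changes how surgeons close the wound. The data are few, and photographs may make them fewer. An imprecise interaction near zero could be read as reassurance when the same data, analysed directly, would be more informative.

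**Working it through.** **Inputs from the protocol article**
- Trial duration: "randomising the target number of 330 participants in nine months".
- Sample size: 920 eligible; "Assuming a 36% recruitment rate and 110 randomised participants per group, a 90% adherence rate will be estimated with a 95% CI of 82–95".
- Randomisation: three dressings by two disclosure times, giving six groups.

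**Assumptions, because the article gives no figure**
- 1:1 timing allocation, so 330/6 = 55 per cell.
- Two-sided 5% level and 80% power, so the multiplier is 1.960 + 0.842 = 2.802.
- A binary closure feature near 50%, so the variance per participant is 0.25. The ratio found below does not depend on this choice.

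**The plan's own figures.** 0.36 × 920 = 331, against the stated 330. The 95% interval for 330/920 is 32.8–39.0%, for 552/920 it is 56.8–63.2%, and for 99/110 (exact) it is 82.8–94.9%. The printed limits (32–39, 56–64, 82–95) agree to within one point. None of them concerns closure.

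**Target.** Let δ be the difference in closure between two dressing groups caused by knowing the allocation.
- Before-closure arm: the expected difference is δ.
- After-closure arm: the expected difference is 0 if disclosure timing is kept.
- Interaction: δ − 0 = δ.

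**Variance, with n = 55 per cell**
- Before-closure contrast: 2σ²/55 = 0.0364σ².
- Interaction: 4σ²/55 = 0.0727σ².
- Ratio: 2.0. The two-degree-of-freedom comparison of all three dressings gives the same ratio.

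**On the percentage scale**

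| | Before-closure contrast | Interaction |
|---|---|---|
| Standard error | √(2 × 0.25/55) = 9.5 points | √(4 × 0.25/55) = 13.5 points |
| Detectable at 80% power (× 2.802) | 27 points | 38 points |
| Power for a 25-point shift (0.5 SD) | 75% | 46% |
| Power for a 10-point shift | 18% | 11% |

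A simulation of a shift from 45% to 70% in one disclosed group (20,000 replicates) gave 77% and 47%.

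**Photographs.** If only half the participants had usable photographs (an assumed share), cells would hold 27.5. The detectable differences would rise by √2, to about 38 and 53 points.

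**Leakage.** If a share λ of the after-closure arm learned the allocation early, the interaction would target (1 − λ)δ and need 2/(1 − λ)² times the information of the before-closure contrast: 2.5, 3.1 and 4.1 times at λ = 10%, 20% and 30%. The before-closure contrast is unaffected, because it does not use the after-closure arm.

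**If the group comparison means dressing groups pooled over timing.** Its expected value is (δ + 0)/2 = δ/2, with standard error √(2 × 0.25/110) = 6.7 points. Rescaled to δ, that is 13.5 points, the same as the interaction.

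**The case against.** The best case for the plan has four parts.

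- **The interaction is valid.** It is an unbiased way to ask whether disclosure changes dressing-specific closure. It is offered as an exploratory subgroup analysis in a pilot, with no power claim and no decision rule, and such an analysis would normally show the timing-specific dressing differences as well. This stands, and it limits the point to precision and emphasis. It does not make the noisier contrast the better one to name.
- **The order of contrasts belongs in an analysis plan.** Partly so. But the article does name a specific contrast for closure, and a more precise one is available from the same data.
- **Zero by design depends on conduct.** Correct: disclosure timing is measured because it may not be kept. As shown, leakage weakens the interaction further and leaves the before-closure contrast valid by randomisation.
- **The gain does not rescue the pilot.** Also correct. Neither analysis would reliably find a 10-point shift.

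Three stronger readings are tempting and not supported. A reader might infer that the plan compares dressing groups pooled over timing. The article does not say so: the groups could equally be the six cells, which would already contain the contrast wanted here, or the two timing arms, which ask a different question to which the factor of two does not apply. A reader might infer that a null result would lead the main trial to disclose early, but no passage makes that link. And a reader might see one disclosed group (55) against the whole after-closure arm (165), with standard error √(0.25/55 + 0.25/165) = 7.8 points, as a sharper version of the same contrast. It is not, because it mixes any general effect of early disclosure with a dressing-specific one.

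**Conclusion.** The point holds as a matter of efficiency. For equal cells and kept disclosure timing, the named interaction estimates the same quantity as the before-closure dressing contrast with exactly twice the variance. At an assumed 55 per cell and a feature near 50%, that is a detectable difference of about 38 points instead of 27. The factor of two does not depend on the outcome's variance, the significance level or the effect size. The percentage figures do, and they also rest on the assumed 1:1 timing ratio. The planned analysis is not biased, and the documents do not establish that it pools over timing. This is a worthwhile, low-cost improvement to an exploratory analysis.

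**What to change.** In the Statistical analyses section:

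1. Make the dressing-group differences within the before-closure arm the main estimate of performance bias in closure. Analyse by randomised disclosure arm and adjust for the stratification factors, Trust and specialty.
2. Report the dressing difference in the after-closure arm as a check that concealment held, alongside the planned outcome on adherence to disclosure timing.
3. Keep the timing-by-dressing interaction as supportive.
4. State which groups the general closure comparison refers to. If it is dressing groups pooled over timing, do not read it as evidence on performance bias, because it halves the effect.
5. If a disclosed group is compared with the whole after-closure arm, report this separately as the effect of disclosing that allocation early.
6. Give all estimates with confidence intervals, and do not read a null result as excluding modest shifts.

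The cost is a few lines of analysis wording. Data collection and trial conduct do not change.

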### Dissemination

The results of the pilot trial will be reported in peer-reviewed journals, in a report to the funder and as a lay summary to participants. We will apply authorship criteria established by the International Committee of Medical Journal Editors.

### Changes to the protocol since first approved

This paper describes protocol version 5 (21 October 2016). Two substantial amendments have been approved.

Version 2 was the first approved protocol. The first amendment (from v2 to v3) was approved (8 December 2015) before starting to recruit. Due to the short duration of the pilot trial, REC approval was obtained for a design as conceived at the outset for the study, before Phase A was completed. The first amendment described revisions to this protocol that were required as a result of the findings from Phase A [16]. The funding application for the study always envisaged that Phase B would be informed by Phase A. The time constraints for the overall study (both Phase A and Phase B), combined with the time needed to obtain REC approval, made it inevitable that an amendment would be required after Phase A ended. This amendment included: changing the trial population to include patients having unplanned operations; substituting the intervention of a complex dressing with glue-as-a-dressing; and addition of the WMQ and WEQ as secondary outcomes.

The need for a second amendment (v3 to v4, then to v5 to accommodate a change requested by the REC) arose from initial difficulties in recruiting patients having unplanned surgery and obtaining patient-reported follow-up questionnaires. This amendment (approved 6 September 2016) substituted a 4-h period between giving the PIL to a potential participant and requesting consent by the statement ‘as long as possible’, qualifying this as ‘usually more than 4 hours for elective surgery and usually more than 1 hour for unplanned surgery’. We justified this on the basis of feedback from trainee surgeons and research nurses that potential participants did not require ‘thinking time’ in order to decide whether to take part. We also revised the protocol to allow the 4–8-week WHQ to be administered over the telephone by a health professional, as well as face-to-face. We applied for the trial to be adopted by the Health Research Authority shortly after submitting the amendment, in order to obtain approval for another NHS Trust to recruit patients having abdominal surgery.

